#### Summarizing Adverse Events

| Measure                                     |
|---------------------------------------------|
| Fall                                        |
| Delirium                                    |
| Potentially preventable VTE                 |
| New pressure ulcer                          |
| Thrombophlebitis at peripheral IV site      |
| CAUTI                                       |
| New Clostridium difficile                   |
| New MRSA                                    |
| New arrhythmia                              |
| Hypokalemia                                 |
| Acute kidney injury                         |
| Transfer back to hospital                   |
| Mortality (unplanned) during admission      |
| Mortality (unplanned) 30-day post-discharge |

#### ***Early transfer to home hospital vs traditional hospital***

We plan to use the same statistical analysis as in the Standard Home Hospitalization methods noted above. However, we do anticipate requiring an additional variable that notes whether a patient was initially considered for home hospital care and was not eligible due to a full census, and then was later taken home when the home hospital service census allowed.

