  - When surrogate consent is relied upon, assent of the subject will be a requirement for participation in the research unless the subject is incapable of giving assent due to his/her medical condition. If the individual objects to participation, s/he will not be enrolled.
  - In the case of surrogate consent, a patient must be returning to their prior level of supervision.
- For patients already on the hospital floor: Previously, we had only allowed patients who had been admitted for less than 24 hours to be home hospitalized. We now wish to expand this criterion to patients at any timepoint in their hospitalization. We believe that many patients may benefit from home hospital care, irrespective of how long they have been traditionally

hospitalized. Enrollment will proceed exactly as in the emergency department, with the exception that it will need to be assessed and reassessed daily with an inpatient team to determine the time at which the patient has a stable acute care plan that meets all of the above criteria. That is, the patient is clinically improving, has continued low probability of clinical deterioration or need for an invasive procedure, but still requires acute care.

- Subjects who do not speak English will use a short-form consent form with the assistance of a certified telephone interpreter.

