## Statistical methods

### *Home hospital vs traditional hospital*

#### *Quantitative*

We plan to form 3 different control groups (with groups listed in order of preference):

1. Patients who were deemed eligible for home hospital, but the service was full (and they were not enrolled subsequently if the service was no longer full);
2. Patients who were deemed eligible for home hospital, but lived outside of the 7.5-mile catchment area; and
3. Patients who were admitted to the hospital.

For each control group, we will use propensity score weighting, adjusting for covariates of interest (see table above), baseline functional status, and DRG. We will be cognizant of over-adjustment depending on our final sample size for each group above. If possible, we will use only group 1 above, as it is the strongest. If we have insufficient control group sample size, we may choose to combine groups 1 and 2 above.

The primary outcome (hospitalization cost) will be assessed using a generalized linear model assuming a gamma distribution with a log link. We will use a multivariable regression approach for secondary

outcomes, using logistic regression for binary outcomes and non-transformed linear regression for normally distributed continuous outcomes as appropriate.

We *a priori* plan to perform a subgroup analysis that does not involve any outlier participants, should this occur. We also *a priori* plan subgroup analyses by diagnosis, by age group, by disposition, by location of admission (e.g., ED, floor, clinic, and home), and by daily activity level. We also *a priori* plan to analyze our outcomes with means, but also with median and interquartile ranges, which are less subject to outlier effects. We may choose to employ non-parametric tests of significance should our data be nonparametric.

We *a priori* plan to adjust our secondary analyses using the Benjamini-Hochberg method. We *a priori* choose a false-discovery rate of 0.20.

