### *Remote vs In-Person Care Analysis*

During our prior RCT of home hospital, patients experienced a mean of 0.09 (SD 0.29) adverse events during their home hospital admission. We believe the smallest clinically meaningful treatment difference would be 0.1 adverse events (i.e., from 0.09 to 0.19 adverse events per patient). In this non-inferiority trial ( $\alpha=0.025$ , power 80%, non-inferiority limit 0.1 events), we would require 210 patients (105 in each arm). Because of clustering, the actual required sample size will be larger. With 5 home hospital physicians ( $\rho$  0.01), we require 260 patients (130 in each arm). We consistently enroll 25 patients monthly, leaving us with sufficient power after about 11 months.

We plan an interim futility analysis. After 130 patients have completed the remote vs in-person care study, we will calculate the difference in adverse event rates between the two arms. If the difference is 0.10 or higher (with the higher rate in the intervention arm), then we will stop the trial for futility. This rule will reduce the power about 2%.

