### *Early Transfer*

To calculate sample size, we used simulation in the PASS program (NCSS LLC, Kaysville, UT) comparing gamma distributed costs, with baseline data based on the home hospital RCT. With 324 patients in each arm of the study, even accounting for intraclass correlation by Home Hospital physician (intraclass correlation coefficient 0.01, cluster size 65), we will have 82% power to detect a relative decrease of 21% in total costs of care, smaller than the 27% decrease seen in this outcome in the Home Hospital RCT and close to the smallest reduction that would be considered clinically important. This sample size will also provide 80% power to detect a 43% reduction in readmission (again smaller than that seen in the Home Hospital RCT), and 81% power to detect non-inferiority for adverse events (assuming a baseline of 0.15 events per patient).

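### Early transfer vs traditional hospital: the added variable can be true only of transferred patients, the preferred controls are chosen on a later event, and no common time zero is set, so the result can be biased in either direction

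*Protocol*

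**What the plan says.** Protocol, Statistical methods, early-transfer paragraph: the analysis is that of the standard home hospitalization comparison, plus a variable marking a patient who "was not eligible due to a full census, and then was later taken home when the home hospital service census allowed".

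The analysis it borrows (Home hospital vs traditional hospital, Quantitative) weights by propensity score on covariates of interest, baseline functional status and DRG. Its preferred control group is eligible patients who found the service full, with the condition "and they were not enrolled subsequently if the service was no longer full".

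The enrollment section removes the former 24-hour limit for floor patients: "We now wish to expand this criterion to patients at any timepoint in their hospitalization". It asks that "the patient is clinically improving, has continued low probability of clinical deterioration".

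In the Study endpoints table, the primary outcome of this comparison is cost of the acute episode plus 30 days. Adverse events are secondary and tested for non-inferiority. The Early Transfer power paragraph claims "81% power to detect non-inferiority for adverse events (assuming a baseline of 0.15 events per patient". Neither it nor the methods paragraph says when cost and events begin to count in either arm.

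**The concern.** Three stated rules interact.

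- **The added variable contains the exposure.** Being taken home is what this comparison studies. A variable that requires it is not a baseline characteristic and has no counterpart among controls.
- **Patients turned away for a full service are divided by what happens next.** Those who later get a place are treated; those who never do form the preferred controls. Getting a place depends on still being in hospital when one opens and on improving by then. Covariates measured at admission cannot undo that.
- **Transfer can come on any day, but no time zero is named.** The borrowed analysis was written for a study that also enrolls at presentation, where the question hardly arises. Here it decides which days and events belong to which arm.

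At stake are a safety claim of non-inferiority and the primary cost result, powered for a 21% reduction.

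**Working it through.** **1. The plan's power figure.** Inputs: "With 324 patients in each arm of the study" and "intraclass correlation coefficient 0.01, cluster size 65". Design effect = 1 + 64 × 0.01 = 1.64; effective n = 324 / 1.64 = 197.6 per arm. The paragraph gives no margin or alpha, so I borrow "non-inferiority limit 0.1 events" and alpha 0.025 from the remote-care power section.

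Power = Φ(margin / SE − z), with SE = √(2 × variance / 197.6).

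- Binary variance 0.15 × 0.85 = 0.1275, one-sided 0.025: SE 0.0359; Φ(2.78 − 1.96) = 79.5%.
- Poisson variance 0.15, one-sided 0.05: SE 0.0390; Φ(2.57 − 1.645) = 82.2%.
- Poisson variance 0.15, one-sided 0.025: 72.8%.

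The stated 81% is thus reproduced approximately, under a borrowed margin. It does not depend on time zero and says nothing about bias.

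**2. The added variable.** Let T = transferred, W = service full when first considered, V = the protocol's variable = W × T. Then P(T = 1 | V = 1) = 1. In the propensity model there is no overlap at V = 1.

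In an outcome model with T and V, the T coefficient compares transferred patients with V = 0 against all controls. Suppose no true effect, W patients carrying r times the risk of others, and a share p of controls with W = 1. The T rate ratio is then 1 / (1 − p + p·r).

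| Assumed p | r = 0.7 | r = 1 | r = 1.3 |
|---|---|---|---|
| 0.5 | 1/0.85 = 1.18 | 1.00 | 1/1.15 = 0.87 |
| 1 (control group 1 alone) | 1/0.7 = 1.43 | 1.00 | 1/1.3 = 0.77 |

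A simulated null Poisson fit gave 1.19 and 0.86 for r = 0.7 and 1.3, which corresponds to p slightly above one half. With W in place of V it gave 1.00 in both cases.

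**3. Time zero, by hand.** Assumptions, not in the protocol: stay = 1 + N with N Poisson(4), mean 5 days; 0.03 events per day, so 5 × 0.03 = 0.15, the plan's baseline; transfer after day k if still admitted, regardless of earlier events; no true effect.

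E[stay | stay > k] = 1 + E[N | N ≥ k]:

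- k = 1: 1 + 4/0.9817 = 5.07
- k = 2: 1 + (4 − 0.0733)/0.9084 = 5.32
- k = 3: 1 + (4 − 0.0733 − 2 × 0.1465)/0.7619 = 5.77

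| Events per transferred patient (all admissions: 0.150) | k = 1 | k = 2 | k = 3 |
|---|---|---|---|
| Counted from admission, 0.03 × stay | 0.152 | 0.160 | 0.173 |
| Counted from transfer, 0.03 × (stay − k) | 0.122 | 0.100 | 0.083 |

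Counting from admission puts the transferred arm above 0.150, because only longer stays reach a transfer. Counting it from transfer, against controls from admission, puts it 19% to 45% below. Controls still in hospital on day k and counted from day k have the same 0.122, 0.100 and 0.083, a ratio of 1.00.

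**4. Time zero, by simulation.** Assumptions: gamma stays with shape 2 and mean 5 days; 0.03 events per day; a place offered after 0.5 day plus an exponential wait averaging 1, 2 or 4 days; no true effect.

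| Rule | Wait 1 | Wait 2 | Wait 4 |
|---|---|---|---|
| Transfer only if event-free so far; never-transferred controls | 0.46 | 0.55 | 0.62 |
| Transferred from transfer, all admissions from admission | 0.84 | 0.81 | 0.78 |
| As previous row, plus 2% transfer back | 0.97 | 0.94 | 0.91 |
| Transfer regardless of events, both from admission; all admissions | 1.11 | 1.19 | 1.29 |
| Same; never-transferred controls | 3.78 | 2.67 | 2.09 |
| Same start day in both arms | 1.00 | 1.00 | 1.00 |
| Same start day, plus 2% transfer back | 1.16 | 1.17 | 1.17 |

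The 2% is the appendix figure (5 of 203). Transfer back is in the adverse-event summary list, but the Safety table collects it in the intervention arm only.

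**5. Why cost is exposed.** In the 3.78 case the arms have 0.166 and 0.044 events. Dividing by 0.03 per day gives mean stays of 5.5 and 1.5 days with no treatment effect. In the 2.09 case, 0.193 and 0.092 events give 6.4 and 3.1 days.

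**The case against.** A reader might infer that follow-up starts at transfer in one arm and at admission in the other, and that the comparison must therefore show fewer adverse events at home. The protocol supports neither. Reusing the same analysis refers to the model, not to a time origin, and silence on the origin could be filled by a statistical analysis plan. Nor must a transferred patient be event-free: the criteria ask for stability and improvement, which a patient whose hypokalemia has resolved could meet. Length-biased selection and the home-only transfer-back item push the estimate upward.

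It can also be said that the protocol does not state where the added variable enters, and it might only flag a subgroup. Excluding later-enrolled patients from control group 1 keeps people treated at home out of the hospital arm. Control group 2, outside the catchment, is not selected on later enrollment. Adverse events are secondary here, and the randomized remote-care comparison is untouched.

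All of this stands against a claim of known direction or size. It does not rescue the variable: as worded it is arm-determining wherever it enters a model, and the sentence appears as an addition to a weighted analysis. Nor does it change the fact that the preferred controls are defined by a later event while transfer is open on any day.

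**Conclusion.** The concern holds for three features of the text: a variable that only the transferred arm can have, a preferred control group conditioned on not being enrolled later, and no common time zero despite transfer on any day. Together they can bias both the adverse-event non-inferiority result and the primary cost result. The direction is not settled. Null adverse-event rate ratios run from 0.46 to 3.78 across the rules tested, and adjusting for the added variable alone can move the estimate either way. These sizes rest on assumed stays, waits, a constant event rate and assumed risk differences; they show what is possible and do not predict the result. No size was derived for cost itself. The stated 81% power is unaffected. This should be corrected before the analysis is run.

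**What to change.** - Replace the added variable with a baseline indicator, service full when first considered (yes/no), recorded by the same definition in both arms. In control group 1 every patient scores yes. If that group is used alone, restrict the weighted comparison to transferred patients who also score yes.
- Set time zero as the hospital day of transfer. Compare each transferred patient with patients still in hospital and meeting the transfer criteria on that same hospital day. Count cost and events from that day in both arms.
- Let a patient transferred later serve as a control only until transfer, then censor. Simply keeping such patients in control group 1 throughout would place treated patients in their own control arm.
- Report adverse events also without transfer back to hospital, which only home patients can have.
- State the adverse-event margin and alpha for this comparison.

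Cost: wording and modest analysis programming in an evaluation that is already retrospective and weighted; participants are unaffected. The daily reassessment in the enrollment section covers candidates for enrollment and is not shown to be recorded for controls, so their eligibility on the matched day may have to be approximated from existing records.

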#### ***Paramedic Analysis***

In a retrospective analysis, we plan to measure the difference in our slate of cost, quality, safety, and experience measures (above) between patients who were cared for when the paramedic was part of the care team vs patients who did not have an interaction with the paramedic. We plan to use the same statistical analysis as in the Standard Home Hospitalization methods noted above.

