### Rationale

Our encouraging outcomes, coupled with the hospital's ongoing capacity concerns, led the hospital to require a single-arm intervention-only home hospital study for our current slate of included conditions that began in January, 2018. We have enrolled over 300 patients since January, 2018 very successfully and have consistently presented our safety data for the Committee's review. With our present local

data, compounded by the plethora of international studies cited above, we believe we have shown that home hospitalization delivers a reasonable substitute to hospitalization for correctly selected patients.

We seek to continue and expand this work in the context of IRB approval for several reasons, including the continued ability to

- employ devices in off-label uses. For example, the IRB previously approved the use of a wireless patch to record and report on vital signs. We continue to benefit from use of this device. We seek to deploy additional technologies to the home, all described below.
- deploy novel personnel. For example, the IRB previously approved the use of paramedics in our home hospital team. We intend to continue our use of paramedics, described below, and test in a retrospective pre/post design the impact of our already-deployed home hospital paramedic on safety and patient experience.
- Prospectively collect and report on a battery of outcomes, many of which are first-in-class and will benefit from additional sample size. For example, the IRB previously approved collection of daily steps.
- Test remote physician care. In a randomized controlled non-inferiority trial, we will test an in-person daily physician visit (“in-person care;” control) vs a daily physician visit conducted remotely via video facilitated by a care team member (“remote care;” intervention) for patients who are home hospitalized. For patients in the remote care arm, the physician can pragmatically choose to see a patient in-person based on the clinical context.

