| Monitoring    | Wireless remote vital signs, telemetry, activity tracking, sleep tracking, predictive analytics for deterioration                                                                                                                                                                                                                                                                                                                                                                                                                                                                                                                                                                                                                             |

As denoted in the figure above, the physician will make at least one daily interaction with the patient. The nature of this interaction will be guided by the control versus intervention arm, and the physician's discretion. If the patient is in the control arm, the physician will make a daily in-person visit (usual care). If the patient is in the intervention arm, the physician sees the patient remotely via facilitated video, including near-real-time transmission of heart, lung, and abdominal sounds as needed. The nurse or paramedic seeing the patient will facilitate a physical exam and discussion with the patient. If the physician chooses for clinical purposes, s/he may still see the patient in-person. At the discretion of the physician, paramedic, and nurse, the physician can make additional visits should the patient's clinical condition require it. The nurse or paramedic will make at least two daily visits to the patient's home. At the discretion of the physician, paramedic, and nurse, the nurse or paramedic can make additional visits should the patient's clinical condition require it. This will be an ongoing twice daily discussion among clinicians, patient, and caregivers, as applicable.

As denoted in the figure above, a patient or clinician can initiate a video or in-person visit at any time.

As denoted in the figure above, a home health aide may be deployed. If deemed necessary by the home hospital attending, patient, and/or caregivers, the home hospital program can provide an on-demand home health aide that can provide care in 12 hour shifts.

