| Paramedic + nurse care vs nurse care alone              | Retrospective, non-inferiority, propensity-weighted evaluation               | Number of adverse events                              | Unplanned readmission after index, y/n
Picker experience questionnaire
Global experience score
Personnel costs           |

\*Non-inferiority for this outcome

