### *Remote vs In-Person Physician Care*

In a randomized controlled non-inferiority trial, we will test an in-person daily physician visit (“in-person care;” control) vs a daily physician visit conducted remotely via video facilitated by a care team member (“remote care;” intervention) for acutely ill patients who are home hospitalized. The primary outcome (dependent variable) is number of adverse events during the acute episode of care (see “Summarizing Adverse Events” table below). The primary predictor (independent variable) is study arm (in-person care vs remote care). We will assess the non-inferiority of the primary outcome with a generalized linear model using Poisson distribution, given the primary outcome is count data. Although we have multiple covariates of interest, we are cognizant of over adjustment. We plan to adjust for age, gender, race/ethnicity, PRISMA-7, education, and HOSPITAL score). We may include additional covariates if groups have significant differences at baseline.

Because patients in the intervention arm will receive at least some of their intervention through a “change agent” (in this case, a Home Hospital team) shared with other participants, we need to account for this in the analysis. We will therefore cluster by Home Hospital physician using general estimating equations.

Other outcomes will be analyzed in a similar manner, using Poisson regression for other “count” outcomes (e.g., number of new or worsening signs or symptoms per patient, days at home since discharge), multivariable logistic regression for binary outcomes (e.g., 30-day readmission, ED visit, PCP

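### Paramedic analysis: one group is defined by era and the other by individual contact, so read literally they overlap, contradict the pre/post design and admit selection on length of stay; the outcome also has no count model

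*Protocol*

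**What the plan says.** The protocol describes the paramedic comparison in three places.

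- Rationale: the aim is to "test in a retrospective pre/post design the impact of our already-deployed home hospital paramedic on safety and patient experience".
- Study endpoints table: the contrast is "Paramedic + nurse care vs nurse care alone", the type is "Retrospective, non-inferiority, propensity-weighted evaluation", and the primary endpoint is the number of adverse events.
- Statistical methods, Paramedic Analysis: one group is "patients who were cared for when the paramedic was part of the care team"; the other is introduced by "vs patients who did not have an interaction with the paramedic". The analysis is to follow the home hospital versus traditional hospital methods.

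Those methods weight by a propensity score built from the covariates table, baseline function and DRG. They then name a gamma model for cost, logistic regression for binary outcomes and linear regression for normally distributed outcomes, and allow non-parametric tests.

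On exposure to the paramedic, Study visits and measured parameters says "The nurse or paramedic will make at least two daily visits" and that "the nurse or paramedic can make additional visits should the patient's clinical condition require it".

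The Power analysis gives the paramedic study no figures of its own and refers to the calculations for the other studies.

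**The concern.** The two halves of the comparison rest on different bases. Treatment while the paramedic was on the team is a calendar or team property, known at admission. Not having interacted with the paramedic is an individual event, known only once the stay is over. The text does not confine the comparator to the period before deployment and has no rule for era patients who were never visited.

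This matters because lack of contact is not neutral. Each further day brings at least two more visits by a nurse or paramedic, so patients without contact tend to be those with short stays, and short stays leave less time for an adverse event to be counted. Weighting on characteristics at admission does not undo selection on something that happens later. The comparison is a non-inferiority test on safety, done retrospectively. An analyst could therefore choose between groupings with the outcomes in hand, and part of any difference could come from the grouping alone.

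**Working it through.** **Step 1. Set the definitions side by side.**

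| Patient | Paramedic group (era or team) | Comparator (no contact) | Pre/post design in Rationale |
|---|---|---|---|
| Treated before deployment | no | yes | pre |
| Treated after deployment, visited by paramedic | yes | no | post |
| Treated after deployment, never visited | yes | yes | post |

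The third row is the overlap. The label in the endpoints table does not say whether era or contact decides it.

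**Step 2. Check whether the planned weighting could repair it.** Neither length of stay nor calendar time is in the adjustment set. The covariates are taken at admission, except for a readmission risk score taken at discharge and a 30-day repeat of caregiver burden. Where the protocol defines the outcome, in the remote versus in-person section, it is the "number of adverse events during the acute episode of care", so a longer stay means more time at risk.

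**Step 3. Size under no paramedic effect.** The protocol states no figure for this analysis, so there is none to reproduce. From the document: a mean of 0.09 events per admission and a limit of 0.1 events (Power analysis, Remote vs In-Person Care Analysis), and at least two visits a day. All other inputs are assumptions.

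*Model A, which can be solved by hand.* Stay is 1 + Poisson(3.5) days (mean 4.5), with 0.02 events per day for everyone (4.5 × 0.02 = 0.09) and a daily chance p of a paramedic visit.

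- Share of era patients without contact: f = (1 − p)·exp(−3.5p).
- Their mean events: m0 = 0.02·[1 + 3.5(1 − p)].
- Comparator mean with r pre-era patients per era patient: (0.09r + f·m0)/(r + f).
- Spurious difference: 0.09 minus the comparator mean, when the paramedic group is all era patients.

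| p | f | m0 | Difference, r = 1 | Difference, r = 0 |
|---|---|---|---|---|
| 0.3 | 24.5% | 0.069 | 0.004 | 0.021 |
| 0.5 | 8.7% | 0.055 | 0.003 | 0.035 |
| 0.7 | 2.6% | 0.041 | 0.001 | 0.049 |

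Example for p = 0.3, r = 1: (0.09 + 0.245 × 0.069)/1.245 = 0.0859, and 0.09 − 0.0859 = 0.004.

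*Model B, simulated over wider ranges.* Stay is 1 + negative binomial (k = 2) with mean 3, 4.5 or 6 days. There are two visits a day, of which the paramedic makes a share s of 10%, 25% or 50%, so P(no contact | stay L) = (1 − s)^(2L). Events are scaled to 0.09 per stay.

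- Era patients without contact: 3% to 57%. Their mean stay is 1.3 to 3.8 days, against 3.2 to 7.4 days in contacted patients; their events are 0.021 to 0.071, against 0.093 to 0.116.
- Spurious difference, all era patients against the comparator: 0.002 to 0.009 for r = 1, 0.004 to 0.014 for r = 0.5, and 0.019 to 0.069 for r = 0.
- Central case (mean stay 4.5 days, s = 25%): f = 0.180 and m0 = 0.0424. For r = 1 the comparator mean is (0.09 + 0.180 × 0.0424)/1.180 = 0.0827, a difference of 0.007. For r = 0 the difference is 0.09 − 0.0424 = 0.048.
- If the paramedic group is instead limited to contacted patients, r = 1 gives about 0.005 to 0.033.

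With both groups set by calendar period, the expected difference under either model is zero.

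**Step 4. Check the method reference.** The primary endpoint is a count. At a mean of 0.09, a Poisson count is zero in exp(−0.09) = 91% of patients. The methods referred to name no model for counts and no non-inferiority procedure. The remote versus in-person section specifies Poisson regression for this same outcome.

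**The case against.** The best defence is that the Rationale already names a pre/post design. If lack of interaction is simply shorthand for treatment before deployment, the groups are disjoint and nothing is selected on stay. A second coherent reading is seen versus not seen by the paramedic, which also gives disjoint groups, although selection on contact then returns. Both readings are possible. Neither is what the section says, and the protocol does not choose between them, so the ambiguity stands.

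On size, the objection largely succeeds. A reader might infer a spurious gap of 0.03 to 0.05 events, or 30% to 50% of the 0.1 limit. In Model A that gap arises only when contacted era patients are compared with uncontacted era patients (for example 0.091 against 0.041 at p = 0.7, where the uncontacted are 2.6% of era patients). That is not the literal comparison, whose comparator also includes every pre-era patient, and a pre/post design implies that such patients exist.

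On direction, short stays make the comparator look safer. That counts against the paramedic group and is conservative for non-inferiority. Extra visits after deterioration would push the same way, but the protocol does not assign paramedics by severity and neither model includes this. Early transfer back to hospital pushes the other way, because it is a listed adverse event that also shortens the stay. No direction can be asserted.

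A reader might also infer that the plan applies a gamma model to event counts. It does not: that model is assigned to cost only. A full model specification may be left to an analysis plan. What remains is that this section points to methods that do not cover its primary endpoint, while another section of the same protocol does.

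**Conclusion.** The inconsistency is established from the text. As worded, the groups overlap and do not match the stated pre/post design, and the comparator admits era patients selected on a post-admission event that the planned weighting cannot correct.

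The resulting bias cannot be fixed from the documents. It depends on the paramedic's share of visits, the distribution of stay and the number of pre-era patients, none of which is given. Under the assumptions shown, and with all era patients as the paramedic group, it is about 0.001 to 0.009 events per patient with equal numbers of pre-era and era patients. With no pre-era patients it is about 0.02 to 0.07, or 0.048 in the central case. Against a limit of 0.1, that runs from negligible to more than half. The direction is uncertain.

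The missing count model and non-inferiority procedure are a separate, smaller defect. This is a retrospective side analysis, and the randomised comparison is unaffected. The point should still be corrected, because it concerns a primary safety endpoint and the repair is cheap.

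**What to change.** - Define both groups by admission date, before versus after the paramedic joined the team, regardless of contact. Say explicitly that era patients never visited belong to the paramedic group. This is the basis the Rationale already states.
- Adjust for calendar time where feasible.
- Analyse the number of adverse events with the Poisson model of the remote versus in-person section, in place of the reference to the home hospital versus traditional hospital methods.
- State the non-inferiority margin and its scale. The only numeric one in the protocol is 0.1 events per patient, in the power analysis for the remote versus in-person study.
- If a contact-based comparison is kept as a supplement, account for days of stay, for example as an offset.

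The cost is protocol wording; no new data are needed. Era patients without contact dilute any paramedic effect, and in a non-inferiority setting dilution can favour a finding of no difference, so their proportion should be reported. A calendar-time term is closely tied to the before/after indicator, so some calendar-time confounding will remain.
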